##### Self-report measures of the treatment targets and mechanisms

This study uses PIPR, pupil dilation, and EEG because they are relatively inexpensive, and clinical settings could feasibly gain access to a pupilometer or EEG equipment to assess whether the intervention engages associated change mechanisms. However, questionnaire measures tapping similar constructs such as chronotype/circadian entrainment, seasonal beliefs, and depressogenic core beliefs will be included in the pre-, mid-, and post-treatment and follow-up assessment battery and assessed for concordance with the biomarker measures: Composite Scale of Morningness [57], Seasonal Beliefs Questionnaire [32], and the Dysfunctional Attitudes Scale-Form A [55]. Behavioral activation is explored as another potential target and mechanism of CBT-SAD using the Behavioral Activation for Depression Scale (BADS) [56].

##### Winter 2 and 3 follow-up procedures

Follow-up assessments will occur in January of the next two winters (in winters 2 and 3). Testing in January reflects when the vast majority of SAD patients are in episode and when there are sufficient weeks left in the winter to treat them with the alternate modality if we detect a recurrence (i.e., 100% of SAD patients had an annual pattern of depression onset between September and January, 0% remitted before January, and only 22% remitted in January or February) [1]. Consistent with intent-to-treat principles, we will attempt to collect data on all enrolled subjects, including dropouts and those withdrawn from protocol. Participants will be interviewed by a clinical graduate student blind rater with the SIGH-SAD and the SCID-5-RV mood disorders module to assess for a major depressive episode in the interval from treatment endpoint to winter 2 and from winter 2 to winter 3. Participants will be assessed on biomarkers, questionnaire outcomes (BDI-II, BAI, Q-LES-Q, SDS, and MOS-SF-20), and the questionnaires we used in our prior studies to assess treatment utilization in the interim.

### Plans to promote participant retention and complete follow-up {18b}

We will attempt to follow all enrolled participants, including participants who do not complete the treatment or were withdrawn from protocol, consistent with the intent-to-treat principal. This strategy should reduce the frequency of missing data at all time points. In addition, we will implement the tracking and retention strategies that were successfully implemented in the P.I.’s previously completed R01 study where we had very little missing data.

Enrollment will be monitored in weekly team meetings at P.I.’s laboratory, starting the first week of September and continuing each fall/winter season until that year’s recruitment cycle is complete. We will review the number of enrolled participants (overall and the breakdown by sex and race/ethnicity), the number of individuals scheduled for screening in the next week, and the number of individuals who consented but did not qualify based on screening. The project coordinator will maintain a database of our enrolled participants to track the scheduled next study-related visit and the date. Participants who miss an assessment will be called immediately to find out the reason, attempt to reschedule, and encourage their continued participation.

We will attempt to contact subjects lost to follow-up and find out what the barriers are in order to develop ways to address them. Each qualified participant will routinely provide his/her permanent address; all active phone numbers (cell, home, work); email address; and the names and contact information for three people who will know their address and phone number should they move. To maximize sample retention over the interim between study treatment completion in winter 1 and the winter 2 follow-up and between the winter 2 and 3 follow-ups, we will mail each participant a “Stay in Contact” postcard in the fall, a generic holiday card in December, a “Happy Birthday” card on their birthday, and a study newsletter in the spring. The study newsletter will summarize the study without discussing any findings so as not to contaminate subsequent data collection. The purpose of these mailings is two-fold: [1] to maintain rapport and contact with participants as is critical for follow-up evaluations and [2] to maintain current information on participants’ addresses, phone numbers, and email addresses. Participants will be instructed to return the Stay in Contact card with any new contact information. If any mailing is returned unopened, we will attempt to reach the participant by email and phone to verify his/her current address. If we make contact, we will record the correct address in our database. If we cannot reach the participant, we will try to reach the participant by contacting the three people identified by the participant. If we cannot reach a participant through their contact persons, we will use directory assistance and the internet to attempt to locate them.

### Data management {19}

Information about eligibility screening, recruitment, and enrollment will be recorded in an Excel spreadsheet by the Project Coordinator. A separate spreadsheet will be maintained for enrolled subjects and will include subject identification numbers, assigned when a subject meets all eligibility criteria. This spreadsheet will be used to keep track of data collection throughout a subject’s participation in the study, including the dates measures are administered at baseline, during treatment, and at follow-ups. Study personnel will complete all study forms, except those designated for completion by participants. The research assistants will be designated as reviewers of all completed forms for each participant (many of which they will administer anyway) to verify accuracy and completeness before data entry.

The project coordinator will be responsible for data entry, and a graduate student research assistant will be assigned as a second data enterer to circumvent problems related to double data entry by the same person. All data will be independently double-keyed (once by the project coordinator and a second time by the Graduate Student Research Assistant), electronically compared by Co-I/biostatistician (P.M.V.), and reconciled for any discrepancies. No identifiers except subject number will be included in the database files, which will be transferred electronically between the project coordinator and project statistician using encryption software. Each data collection instrument will be entered into a separate data file and will include a sequence number reflecting the measurement schedule, in addition to the date the instrument was administered, to facilitate data linkage and identification of missed measurements. Data will be read into SAS data files and screened for missing, invalid, or illogical values. A written report of questionable data will be sent to clinical study staff for resolution and any unresolved errors will be re-coded as missing. The report will also include a summary of the data received for each subject, so that study staff can check this against their data collection spreadsheet to verify that all data was transferred, entered, and processed.

Individual data files will be named to reflect the data collection instrument and version, so that corrected and updated data files can be compared to earlier versions to verify corrections and numbers of subjects. Backup copies of all files will be written to CD at the time of their creation. Data files will be linked for statistical analyses by subject identification number and measurement schedule sequence number. Treatment group assignment will be identified by linkage to a file associating this information to subject identification number, which will be generated at the time of enrollment. A summary of each subject’s treatment condition will be sent to study staff for confirmation. Data files will regularly be backed up on our University network, where our lab group has a protected-access folder.

It will be important to carefully separate data collection done by observers unmasked to treatment assignment from that done by observers who have to remain masked. Primarily, this will be accomplished by unmasked observers refraining from discussing individual participant treatment assignments in the routine course of the study, participants agreeing to refrain from discussing their treatment with study personnel other than their interventionist, and by separate storage of treatment assignment in the randomization system files, inaccessible to all but designated study personnel for pre-specified purposes. The assigned study treatment code will not be transferred to the main study database to maintain masking of personnel who will be doing data entry, editing, and coding. The Project Statistician will extract a file of treatment assignments from the randomization system at weekly intervals for both data quality assurance and data monitoring. Files merging treatment assignment with participant data will be kept separate from the main database and will not be accessible by masked personnel. Subjects will be given an anonymous identification number that will not be linked to the randomization assignment until the final data analysis. Our database will contain none of the 18 HIPPA-protected personal health identifiers (e.g., name, address, phone, date of birth, SSN). Because electronic data is completely de-linked from personal identifiers, participant confidentiality is protected in transferring data between the P.I.’s laboratory, the University of Vermont Biometrics Department, and the University of Pittsburgh.

All data will be collected at the University of Vermont, but biomarker data will be processed by the University of Pittsburgh collaborators (co-investigators P.L.F., K.A.R., and G.J.S.) who have extensive expertise in our chosen biomarkers. Drs. [name] and [name] will train the study staff at the Vermont site in the biomarker data collection procedures. Co-I P.L.F. will oversee the development, implementation, and analysis of the EEG and pupillary measurement in Vermont, and contribute expertise in the analysis of the data for the proposed project including blink correction, interpolation, and automated data collection. [name] will also supervise the Data Manager at the Pittsburgh site in the management of all actigraphy and sleep diary study data, including the development, maintenance, and documentation of data bases for all sleep diary and actigraphy measures. Co-I K.A.R. will specifically be responsible for overseeing the post-illumination pupil response (PIPR) and dim light melatonin onset (DLMO) data management and processing. Co-I G.J.S. will oversee the development of the emotional reactivity tasks, as well as the implementation and analysis of the EEG measures. Once processed and cleaned, final biomarker data will be transferred, as a de-identified database (coded by subject ID numbers), to the Project Biostatistician (P.M.V.) at the Vermont site) for primary analyses.

Effective March 2020 due to the COVID-19 pandemic, all survey measures were moved online using Qualtrics. Each participant is sent a unique link to input responses, and no identifying information is associated with responses. This also removed the need for data entry (and double-data entry) after this change. SIGH-SAD administration was moved from in-person using paper forms to remote videoconference platform with responses entered in REDCap during the live interview.

### Confidentiality {27}

Original data forms will be kept in locked cabinets in the PI’s laboratory (organized by subject ID numbers) and identifiers will be stored separately. We must collect subjects’ names, addresses, telephone numbers, and email addresses to maintain contact, given that our study has a 2-year longitudinal follow-up interval. Only properly authorized and trained individuals who are directly concerned with the study will have access to individually identifiable private information about human subjects: the PI, the project coordinator, the graduate research assistants, the project statistician, members of the Data Safety and Monitoring Board, and members of the University of Vermont IRB (upon audit as part of annual continuing review).

### Plans for collection, laboratory evaluation, and storage of biological specimens for genetic or molecular analysis in this trial/future use {33}

This trial does not involve collecting biological specimens for storage.

## Statistical methods

### Statistical methods for primary and secondary outcomes {20a}

#### Data analysis

##### Aim 1

Logistic regression will be used to assess the effectiveness of treatment with either CBT-SAD or LT on depressive episode recurrence at winter 2. Covariates will be included in some analyses to assess the effect of treatment on outcomes after adjustment for any ongoing treatment reported at follow-up, such as any new treatment, psychotherapy, light therapy use in the CBT-SAD group, and antidepressant medication as in [name] et al. [14]. An intent-to-treat analysis will be conducted, using multiple imputation (MI) of missing next winter SIGH-SAD scores. Imputed scores will be used to classify depression recurrence status for individuals who dropped out or were lost to follow-up. Imputed values will be generated using the fully conditional specification (FCS) method to obtain regression estimates based on baseline and post-treatment SIGH-SAD (and component 21-item HAM-D and atypical subscale scores), demographic variables, comorbidity, and other baseline patient characteristics. Imputation will be done separately for the CBT-SAD and LT groups because data from our prior study indicate that the relationships between some of these variables and next winter recurrence differ in the two treatments. Ten data sets with imputed values will be generated and a dichotomous recurrence variable will be computed for each subject based on SIGH-SAD criteria. Logistic regression models will be fitted to each of the ten data sets and their parameter estimates will be combined using MI inference methods [43]. SAS PROC MI and PROC MIANALYZE will be used to carry out the imputation and analysis. The “missing at random” assumption of the MI analysis is valid if the imputation model is predictive of outcome. However, if we have an appreciable amount of missing data at follow-up, we will perform a sensitivity analysis using the pattern-mixture model approach (NMAR option in SAS 13.1) to assess the validity of the MI results.

Similar analyses will be performed to compare winter 3 outcomes in the CBT-SAD and LT subjects who did not have a winter 2 recurrence. Secondary analyses will examine the effects of treatment adherence within each treatment and the effect of therapist and therapy group within the CBT-SAD condition.

##### Aim 2

To examine mechanistic differences between CBT-SAD and LT, mixed effects linear regression with subject as a random effect will be used to model biomarker changes during treatment as a function of time, treatment, and their interaction. We will also model the relationship between biomarker change and change depressive symptoms as a function of treatment by letting the regression coefficient differ between CBT-SAD and LT. This will provide a test of whether potential mediators of effect are treatment-specific. The predictive value of biomarkers at baseline, their pre-post treatment change, and the persistence of the change at follow-up will be examined using logistic regression (for post-treatment remission and winter 2 recurrence) and linear regression (for SIGH-SAD and BDI-II scores) with post-treatment and winter 2 outcomes as dependent variables. Interactions between the biomarkers and treatment will be used to test if the associations with outcomes differ in the CBT-SAD and LT groups. Adherence will be included in ancillary analyses to test its effect on the relationships of treatment with biomarkers and LT or CBT-SAD outcomes. The relationships between biomarkers and outcomes will be validated by examining how well they predict post-treatment and winter 3 outcomes for subjects who experience a recurrence at winter 2 and are switched to the alternative treatment. Data from the cross-over subjects will also be analyzed using mixed linear regression to compare within-person differences in pre-treatment biomarkers and their changes during their initial and subsequent treatments. Treatment, time point (winter 1 or 2), and their interaction will be included to test the effect of treatment sequence on within-person differences in biomarker responses to CBT-SAD and LT.

##### Aim 3

Logistic and linear regressions similar to those for Aim 1 will be used to compare the effect of switching from CBT-SAD➔LT versus LT➔CBT-SAD on winter 3 recurrence and depression scores. Post hoc adjustment for any differences between switch groups in baseline characteristics, treatment response, and biomarker profiles will be done by including them as covariates. Mixed linear regression will be used to longitudinally model depression scores over the three winters, with treatment as a time-varying covariate.

##### Aim 4

We will test mediating effects of candidate biomarkers on change in depressive symptoms using parallel process latent growth curve modeling (LGCM) [72–74]. These tests will focus on treatment outcomes through winter 2 and winter 3 follow-up to elucidate the mechanisms underlying the long-term benefit of CBT-SAD. Analyses will include all available information from multiple biomarker assessments and multiple assessments of depressive symptoms (on the SIGH-SAD and BDI-II), modeling latent intercept and linear slope factors for individual biomarkers and symptoms. Each biomarker will be analyzed in a separate model to avoid undue model complexity. Parallel process LGCM allows for estimation of indirect effect magnitude from treatment assignment, through change in biomarker, to change in depressive symptoms, as well as the direct effect from treatment to change in symptoms. We will calculate established mediation effect size indices from these models such as proportion of total possible effect mediated [75]. LGCM will be conducted using full-information maximum likelihood estimation in Mplus [76].

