#### Cognitive-behavioral therapy (CBT-SAD)

The P.I. (K.J.R.) tailored traditional CBT for depression to address the special needs of the SAD population in developing the “Coping with the Seasons” protocol and its manual [11]. CBT is placed in a seasonality framework with the rationale addressing the role of environmental changes as well as cognitions and behavior in symptom onset/maintenance. Traditional CBT elements of behavioral activation and cognitive restructuring are framed as ways to improve coping with winter. Some cognitive restructuring specifically focuses on challenging negative thoughts related to the winter season, light availability, and weather. A recurrence-prevention component addresses early identification of negative anticipatory thoughts about winter and SAD-related behavior changes, using the CBT skills learned to cope with future winter seasons, and development of a personalized relapse-prevention plan. As in prior studies, the CBT-SAD protocol includes 90-min. CBT sessions twice a week over 6 weeks (total of 12 sessions and 18 h) in small groups (typically 4–8 patients per group). CBT-SAD sessions were conducted in-person until March 2020, when we moved them to HIPPA-compliant video conference platform due to the COVID-19 pandemic. In our prior R01, CBT-SAD attendance was quite good, mean = 9.1 sessions (SD = 3.5). Seventy-three of 88 (83%) attended 7 or more sessions, and 56/88 (64%) attended 10–12 sessions. To accommodate unpredictable schedules, if a patient misses a session, there is opportunity to “catch-up” with group facilitator before the next session and to make up the session in another concurrent CBT-SAD group; both are documented.

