#### Therapists

Six trained clinical psychology graduate student research assistants will facilitate the CBT-SAD groups, supervised by the P.I. (K.J.R.). Each group will be led by a pair of group facilitators. The P.I. will provide therapists with session-by-session training in the manual content prior to their providing any treatment. Subsequently, PI [name] will review audiotapes of each CBT-SAD session and will discuss these sessions in weekly 1-h group supervision meetings with each pair of facilitators focused on [1] discussion of general issues in therapy, participant progress, and the treatment protocol, and [2] the P.I. providing detailed feedback on the prior two sessions. Supervision and training meetings occurred in person until March 2020 when we shifted to videoconference due to the pandemic, with all parties participating from a private office to protect confidentiality. These training procedures were successfully used to train two community therapists in our prior R01 study, with no significant differences between P.I. [name] and the other two therapists in post-treatment outcomes (all ps > .50). The multi-component supervision protocol reflects what works best in the field [45].

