#### Light therapy (LT)

Participants attend an initial instructional session that follows a script to explain the treatment rationale and assembly/position of the light box. These will be conducted by the (unblinded) P.I. in small groups of 2–4 subjects for efficiency. Effective fall/winter of 2020–2021, the P.I. posted a video recording of the instructional session on the lab’s private YouTube channel for those randomized to light therapy to watch remotely, due to the COVID-19 pandemic. In their homes, LT participants will use the SunRay (SunBox Company, Gaithersburg, MD), a standard device (23” × 15½”× 3¼”) with an ultraviolet shield that emits 10,000-lux of cool-white fluorescent light to the retina when the user is within 18 inches. Each of the 6 weeks, participants will complete the Light Therapy Side Effects Questionnaire used in our prior studies to assess the presence and severity of any side effects attributed to LT and self-reported times for onset of sleepiness, onset/offset of actual sleep, and desired times for onset/offset of sleep over the previous week. Side effects associated with LT are generally mild and can include headache (19%), eyestrain (17%), and feeling “wired” (14%) [46]. Although individuals typically respond within 4 weeks of initiating LT or not at all [16], our LT protocol will be maintained for 6 weeks to match CBT-SAD’s duration. To circumvent ethical concerns of discontinuing LT during the winter (when relapse is likely) [1], participants are encouraged to keep using the light box and bring it to the lab for servicing in May (to check the bulbs against a photometer and download adherence data). In an effort to reduce access to a suitable device as a potential confound, we will offer access to our light boxes to LT participants in winters 2 and 3 and to CBT-SAD participants crossed into LT in winter 2 for use in winter 3.

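### The primary analysis and sample size treat participants as independent although CBT-SAD is delivered in therapy groups; if recurrence is correlated within groups, the standard error of the treatment contrast is understated

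*Protocol article*

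**What the plan says.** **Delivery.** The section Cognitive-behavioral therapy (CBT-SAD) describes 12 sessions of 90 minutes "in small groups (typically 4–8 patients per group"). A participant who misses a session may be able "to make up the session in another concurrent CBT-SAD group". Under Therapists, six graduate students run the groups: "Each group will be led by a pair of group facilitators". Under Light therapy (LT), treatment is individual: "In their homes, LT participants will use the SunRay". The shared element described for LT is one scripted instructional session in groups of 2–4, replaced by a video from fall/winter 2020–2021.

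**Analysis.** In the Data analysis section, the Aim 1 paragraph reads: "Logistic regression will be used to assess the effectiveness of treatment with either CBT-SAD or LT on depressive episode recurrence at winter 2". The model is fitted to ten imputed data sets and the estimates are pooled. Secondary analyses will examine "the effect of therapist and therapy group within the CBT-SAD condition". For Aim 2, "mixed effects linear regression with subject as a random effect will be used to model biomarker changes". Aim 4 uses latent growth curve models fitted by full-information maximum likelihood. No clustered variance is named for any of these.

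**Sample size {14}.** With 80 per arm the trial is said to have 80% power for a 22-point difference, for example 28% versus 50%. With 20% attrition the detectable difference is given as 24 points. No design effect or ICC is stated.

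**The concern.** This is a partially nested design. About 80 CBT-SAD participants sit in roughly 10 (80/8) to 20 (80/4) therapy groups, while LT participants are essentially unclustered. Members of a group share facilitators, 18 hours of sessions and the other members. Delivery also moved from in-person to video in March 2020, which is a further way in which groups can differ.

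Ordinary logistic regression takes each participant as an independent observation. If recurrence is positively correlated within groups, the CBT-SAD proportion is less precise than the model reports. The interval for the treatment contrast is then too narrow, and the test rejects too often under the null. The contrast at stake is the trial's confirmatory superiority test.

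This is more than silence that an analysis plan might fill. The protocol takes up therapy group and places it in a secondary analysis inside one arm. It also names subject as the random effect for Aim 2 and no group effect.

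**Working it through.** **Inputs from the protocol.** 80 per arm; 28% versus 50%; CBT-SAD group size m = 4 to 8; LT treated as unclustered.

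**Assumptions, not in the protocol.** Two-sided alpha of 0.05; ICC from 0 to 0.10; equal group sizes in the formula.

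**1. Reproduce the stated power under independence.** The mean proportion is (0.28 + 0.50)/2 = 0.39.
- Null SE = sqrt(0.39 × 0.61 × 2/80) = 0.0771.
- Alternative SE = sqrt((0.28 × 0.72 + 0.50 × 0.50)/80) = 0.0751.
- z = (0.22 − 1.96 × 0.0771)/0.0751 = 0.92, so power is 82.0%. Exact enumeration of the Wald logistic test gives 81.6%.
- With 64 per arm (80 × 0.8), the difference detectable with 80% power is 24.0 points, which matches the protocol.

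The stated figures therefore reproduce with no design effect.

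**2. Add clustering in the CBT-SAD arm only.**
- Design effect: DE = 1 + (m − 1) × ICC.
- Ratio of true to model SE under the null: sqrt((DE + 1)/2).
- Actual type I error: 2 × (1 − Φ(1.96/ratio)).
- Power of a corrected test: replace the 2 in the null SE by (DE + 1), and multiply 0.28 × 0.72 by DE in the alternative SE.

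Example with m = 6 and ICC = 0.10: DE = 1.50 and the ratio is sqrt(1.25) = 1.118. Type I error is 2 × (1 − Φ(1.753)) = 8.0%. Corrected z = (0.22 − 1.96 × 0.0862)/0.0831 = 0.61, so power is 73.0%.

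| ICC | m | DE | SE ratio | Type I error | Power, corrected test |
|---|---|---|---|---|---|
| 0 | any | 1.00 | 1.000 | 5.0% | 82.0% |
| 0.01 | 4 / 6 / 8 | 1.03 / 1.05 / 1.07 | 1.007 / 1.012 / 1.017 | 5.2 / 5.3 / 5.4% | 81.5 / 81.1 / 80.7% |
| 0.05 | 4 / 6 / 8 | 1.15 / 1.25 / 1.35 | 1.037 / 1.061 / 1.084 | 5.9 / 6.5 / 7.1% | 79.3 / 77.4 / 75.6% |
| 0.10 | 4 / 6 / 8 | 1.30 / 1.50 / 1.70 | 1.072 / 1.118 / 1.162 | 6.8 / 8.0 / 9.2% | 76.5 / 73.0 / 69.7% |

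**3. Check by simulation.** Beta-binomial groups, 200,000 runs per cell, 39% recurrence in both arms and a Wald logistic test. Type I error for m = 4 / 6 / 8 is 4.8% in each case at ICC 0; 4.9 / 5.1 / 5.1% at 0.01; 5.6 / 6.2 / 6.8% at 0.05; and 6.6 / 7.7 / 8.9% at 0.10. These run slightly below the formula and show the same pattern.

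**4. Sample size.** Restoring 80% power for 28% versus 50% would need 82 / 86 / 89 per arm at ICC 0.05 and 88 / 95 / 102 at ICC 0.10.

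**5. Check one possible remedy.** A logistic random intercept in the CBT-SAD arm only compares a group-conditional log-odds (CBT-SAD) with a marginal one (LT). With equal true recurrence in both arms and an ICC of 0.05 to 0.10 on the latent scale, the model's log odds ratio is about −0.02 to −0.04 at 37% recurrence. At 28% it is about −0.04 to −0.08. Both lean towards CBT-SAD although there is no difference.

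**The case against.** A reader might infer that the standard error is certainly too small and that type I error certainly exceeds 5%. The protocol does not support that. It reports no ICC for winter 2 recurrence; at ICC 0 there is no inflation, and at 0.01 it is trivial. The figure near 9% needs both ICC 0.10 and every group at 8, the top of the usual range.

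Several features could weaken clustering. The outcome is measured in January of the next winter, roughly a year after treatment and after a period in which participants use the skills without a therapist. Make-up sessions in other groups mean that membership is not strictly nested. In the earlier trial no significant difference was found between the investigator and "the other two therapists in post-treatment outcomes (all ps > .50"). Conversely, LT is not wholly free of grouping, given its initial session in groups of 2–4.

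Nor has the protocol overlooked grouping: the secondary analysis could show whether a group effect exists, and an analysis plan that is not shown might specify the variance estimator.

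What stands of this is that the claim must be conditional and the range must include zero. What does not stand is that the concern disappears. The earlier therapist comparison covers three therapists and post-treatment outcomes, not therapy groups or winter 2 recurrence, and a non-significant test does not establish a zero ICC. A within-arm analysis of group leaves the between-arm standard error as it was.

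**Conclusion.** The point holds as a conditional one and should be fixed. The stated primary analysis and sample size rest on an unstated assumption of zero within-group correlation, which the group format makes doubtful but does not disprove. Over an assumed ICC of 0 to 0.10 with groups of 4 to 8, two-sided type I error is about 5–9%. Corrected power for 28% versus 50% ranges from 82% down to about 70%. These figures assume equal group sizes, no clustering in LT and no extra correlation from facilitator pairs shared across groups. They cannot be narrowed without an ICC from the investigators' own data.

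**What to change.** **Primary analysis.** Replace the ordinary logistic regression by logistic GEE, or logistic regression with cluster-robust standard errors. Cluster CBT-SAD participants by the group in which they started, regardless of make-up sessions, and enter each LT participant as a cluster of one. Use a small-sample correction, since there may be only 10 to 20 CBT-SAD groups. Fit this in each of the ten imputed data sets and pool as already planned.

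**What to avoid.** Do not rely on a logistic random intercept in the CBT-SAD arm only, unless the arm effects are marginalised before they are compared.

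**Other aims.** Add a therapy-group random effect for CBT-SAD to the Aim 2 linear mixed models, where the conditional-versus-marginal problem does not arise. Use cluster-robust standard errors in the Aim 4 growth models.

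**Sample size.** State the independence assumption and show power over a range of ICC values.

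**Cost.** Some analysis-plan wording and a few lines of code. No new data should be needed: attendance and make-up sessions are documented, and the planned secondary analysis already requires group membership. The price is a slightly wider interval and slightly lower power, both close to nil if the ICC is near zero.
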